### Radiotherapy

For conventional radiotherapy, a single dose of 8Gy will be given using a linear accelerator with at least 6 MV photons. Preferably patients are treated using the ICRU guidelines, but there are no restrictions formulated with respect to the radiation technique. Patients should be treated according to the standard treatment protocol per institution.

For stereotactic treatment (1 x 20Gy), patients will be prepared with a dedicated CT simulator in treatment position with an immobilization device as used per institution. Standard position is supine, no prone position is allowed. Scans should be matched with the pretreatment (diagnostic) MRI images as they provide better delineation of the tumor and the spinal cord than the simulator CT scan. Target volumes are defined according to the ICRU Reports 50 and 62 and according to the International Spine Radiosurgery Consortium Consensus Guidelines for Target Volume Definition in Spinal Stereotactic Radiosurgery [20]. Dose-volume-histograms of the spinal cord or cauda equine, as well as from the organs at risk in the vicinity, will be obtained for all patients. For the spinal cord a maximum of 10Gy to 10 % of the spinal cord volume, which is defined as 6 mm above and below the target volume, is tolerated [21]. Circumferential radiation of the esophagus, trachea, great vessels, stomach, bowel, and rectum should be avoided. Patients should not receive chemotherapy or targeted systemic therapy within 14 days of radiotherapy. All palliative therapy and supportive care for disease-related symptoms will be offered to all patients on this trial. Details of these will be collected on case reports forms. Patients who do not achieve a response to radiotherapy, re-irradiation should only be considered 4 weeks after the initial treatment and only for the conventionally (8Gy) treated patients.

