**Methods/Design:**

This study is a multicenter prospective randomized clinical trial comparing conventional radiotherapy (1 x 8Gy) with stereotactic radiotherapy (1 x 20Gy) for pain reduction and quality of life in patients with painful spinal metastases. A total of 386 patients will be randomized between the two treatment groups. Besides pain measured by the Dutch Brief Pain Inventory, quality of life and cost-effectiveness also will be measured. The primary outcome is pain reduction at 6 weeks after treatment. Secondary outcomes will be the time to pain response, duration of pain relief, health-related quality of life and toxicity, as well as cost-effectiveness.

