
Post-treatment diagnostics should be performed according to the institutions routine guidelines. Recurrence of disease should preferably be confirmed using MRI. Tumor growth less than 25 % is classified as stable disease. Data needed for re-irradiation and the occurrence of spinal cord compression and/or fractures, along with data on systemic treatment are collected at 3-month intervals at the institutes.

The pain score will be divided into four response categories for analyses. Complete response (CR) is defined as a pain score of 0 at the treated site, with no concomitant increase in analgesic intake. Partial response (PR) is defined as a pain reduction of 2 or more at the treated side on a scale of 0 to 10 without analgesic increase, or an analgesic reduction of 25 % or more from baseline without an increase in pain. Pain progression (PP) is defined as an increase in pain score of 2 or more above baseline at the treated site with stable analgesic intake or an increase of 25 % or more in analgesic intake compared with baseline with the pain score stable or 1 point above baseline. Stable pain (SP) is defined as any response that is not captured by the complete response, partial response, or pain progression definitions. Responders are defined as CR + PR; nonresponders are defined as PP + SP.

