### Statistical analyses

The primary outcome of interest in this study is a reduction of pain of 2 points at 6 weeks since baseline. The literature shows that in patients with conventional radiotherapy the percentage of patients with pain reduction ranges from 66 % to 72 %. We assume that the percentage of patients with pain reduction is 70 % in the group with conventional radiotherapy compared to 85 % in the group with stereotactic radiotherapy. Therefore, 135 patients are needed in each group to obtain a power of 80 % (Fisher-exact test, two-sided, alpha = 0.05). We adjust for a drop-out rate of 30 % and will include a total of 386 patients. The primary analysis will be the comparison between the two treatment arms of the proportion of patients with pain reduction, defined as a decrease in pain score of at least 2 points from initial pain score, at 6 weeks. Time to pain progression, radiation-induced fracture and/or death will be calculated from date of randomization to the documentation. For the calculation of response, no fixed time interval from the date of randomization will be applied. Response of treatment will be calculated if at least two successive follow-up pain scores are available.

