## Discussion

The aim of this trial is to test the hypothesis that stereotactic radiotherapy gives a better and longer lasting reduction of pain, better local control, and therefore a better quality of life without an increase of treatment-related side effects compared to conventional radiotherapy for symptomatic spinal metastases. Recent trials and reports using SBRT show excellent local control and a fast pain reduction in 1 to 2 weeks when treating painful spinal metastases [8, 10, 11, 22–26]. In recent years, systemic therapies have improved significantly, resulting in a better median survival of incurable patients, that is, with metastasized disease. Therefore, patients nowadays that are irradiated conventionally for spinal vertebral metastases are at a higher risk of local recurrence. The question is whether the conventional treatment is still appropriate for patients with potentially longer life expectancy, for example, patients with oligometastases or patients with tumors responsive to systemic treatments. Oligometastasis is defined as the state in which the patient shows distant relapse in only a limited number of regions. For these patients, a more radical approach could have a major impact on their quality of life and even life expectancy. In addition, stereotactic treatment shows a faster reduction of pain, occurring within 1 to 2 weeks, compared to pain reduction from conventional treatment, which usually occurs in 4 to 6 weeks. Therefore, patients with short life expectancies may also benefit from stereotactic treatment.

Quality of life is an important issue in cancer patients at all stages of disease. Quality of life is affected by many factors such as the disease itself, but also psychological and social factors. In patients with pain, the quality of life can be impaired due to the pain or the disease itself but also by the multiple treatments to which patients are exposed. The minimization of hospital visits is important. Furthermore, the analgesics can give side effects that may have a negative impact on the quality of life. Radiotherapy can reduce pain resulting from bone metastases and reduce analgesic use and it side effect, thereby improving the quality of life [1]. Knowledge of health-related quality of life and its implementation in the treatment options can help to guide patients in making decisions and personalize their treatment.

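### Re-irradiation opens in the 8 Gy arm alone at week 4, before the week-6 primary score, so relief from a second course can count as response to one 8 Gy dose; the bias is toward no difference and its size is unknown

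*Protocol article*

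**What the plan says.** The Radiotherapy section addresses patients who do not respond: "re-irradiation should only be considered 4 weeks after the initial treatment and only for the conventionally (8Gy) treated patients". This sets an earliest time and limits the option to one arm.

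The Statistical analyses section bases the primary comparison on the proportion with pain reduction, "defined as a decrease in pain score of at least 2 points from initial pain score, at 6 weeks". The definition sets no condition on further local treatment. The response categories in Assessment of the endpoints depend on pain and analgesic use only, for example "Complete response (CR) is defined as a pain score of 0 at the treated site, with no concomitant increase in analgesic intake".

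The origin of the six weeks is given in two ways. The Abstract has "The primary outcome is pain reduction at 6 weeks after treatment". The Statistical analyses section has "The primary outcome of interest in this study is a reduction of pain of 2 points at 6 weeks since baseline".

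For response in general, the Statistical analyses section adds: "For the calculation of response, no fixed time interval from the date of randomization will be applied". Assessment of the endpoints states: "Data needed for re-irradiation and the occurrence of spinal cord compression and/or fractures, along with data on systemic treatment are collected at 3-month intervals". The Discussion contrasts a faster effect of stereotactic treatment, "compared to pain reduction from conventional treatment, which usually occurs in 4 to 6 weeks", and the Background gives the same 4-to-6-week interval.

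**The concern.** Two stated rules interact. A second course becomes available to 8 Gy non-responders up to two weeks before the primary score, and the primary definition takes that score at face value. An 8 Gy patient who has not responded at week 4, is re-irradiated and is 2 points better at week 6 counts as a success of the 8 Gy arm. A stereotactic patient in the same position has no such route.

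The article frames its question as 1 x 20 Gy against 1 x 8 Gy. With early re-irradiation, the comparison becomes 20 Gy once against 8 Gy once or, in some non-responders, followed by a second course. That is a different contrast, and it tends to narrow the difference.

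Time to pain response has the same problem. Since no fixed interval limits response, a first improvement after the second course can be dated and credited to the first.

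What is at stake is mainly the reading of a null result: it could not be taken, on its own, to show that a single 8 Gy dose does as well.

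**Working it through.** **1. The plan's own figure.** Inputs from Statistical analyses: 70% against 85%, two-sided Fisher exact test, alpha 0.05, 135 per arm, 30% drop-out, 386 in total. Full enumeration of the Fisher test at 135 per arm gives power 81.0%. The continuity-corrected formula gives 134 per arm. 2 x 135 / (1 − 0.30) = 385.7, rounded up to 386. The sample size is sound.

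**2. The window.** If week 6 runs from treatment (Abstract), re-irradiation can precede the primary score by up to 6 − 4 = 2 weeks. If it runs from a baseline at randomization (one reading of Statistical analyses), any delay from randomization to treatment shortens this.

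**3. Direction.** Only 8 Gy patients without a response are eligible. Provided that a second course does not itself worsen the week-6 score, it can only add 8 Gy responders. The stereotactic rate is untouched, so the difference moves toward zero.

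**4. Size.** Observed 8 Gy rate = 0.70 + a x s x c, where

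- a = proportion ever retreated. The Background gives a ceiling of 24%, over all follow-up and for conventional radiotherapy in general.
- s = share of those retreatments falling before the week-6 score. Not in the documents.
- c = share of those patients who become week-6 responders because of the second course. Not in the documents.

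With a = 0.24, s = 0.10 and c = 0.10 to 0.15, the rise is 0.24 x 0.10 x 0.10 = 0.0024 to 0.24 x 0.10 x 0.15 = 0.0036, that is 0.24 to 0.36 points. With s = 0.25 and c = 0.15 it is 0.24 x 0.25 x 0.15 = 0.009, or 0.9 points. The larger shifts below are shown only for sensitivity.

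| Assumed rise in 8 Gy rate | 8 Gy rate | Difference from 85% | Exact Fisher power, 135 per arm |
|---|---|---|---|
| 0 (plan) | 70.0% | 15.0 points | 81.0% |
| 0.24 points | 70.24% | 14.76 | 79.8% |
| 0.36 points | 70.36% | 14.64 | 79.2% |
| 0.9 points | 70.9% | 14.1 | 76% |
| 1.5 points | 71.5% | 13.5 | 72.7% |
| 3 points | 73.0% | 12.0 | 62.8% |

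Each full point added to the 8 Gy rate costs roughly 5 to 8 points of power. If nobody is re-irradiated before the week-6 score, the first row applies.

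**5. The opposite error.** Suppose every early re-irradiated patient is counted as a non-responder. If 12% of the 8 Gy arm were re-irradiated early (0.24 x 0.50) and 30% of them would have responded anyway, the 8 Gy rate falls by 0.12 x 0.30 = 3.6 points. Both inputs are assumptions at the high end. With true rates equal at 70%, the Fisher test then compares 66.4% with 70%, and its rejection rate rises from 3.7% to 7.7%.

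**The case against.** Several points on the other side have force.

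- **The use of all week-6 scores is legitimate.** It is a treatment-policy analysis, and the handling of intercurrent treatment is often left to an analysis plan, which is not shown here. This stands as a reason to keep the as-observed comparison. It does not remove the point, because the article states both rules and a question about single doses, and does not declare that policy.
- **The re-irradiation sentence is a restriction.** It sets an earliest time and does not schedule a second course at week 4. This stands: early use may be rare.
- **A second course is unlikely to act fully in two weeks.** If it works over the same 4 to 6 weeks, few patients would convert by week 6. This stands, and it favours the low rows of the table.
- **Some dilution may already be in the 70%.** That figure rests on literature rates of 66% to 72%, and whether those include early retreatment cannot be checked from the document.
- **Dates may be recoverable.** The 3-monthly collection and the case report forms for palliative therapy could still record when re-irradiation took place. The data-capture point is therefore secondary.

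A reader might infer a stronger claim: that a large share of control patients will be retreated before week 6 and that power collapses to about 41%. That figure needs an 8 Gy rate of 76%, reached by placing half of a 24% lifetime ceiling in two weeks and having half of those patients convert (0.24 x 0.50 x 0.50 = 0.06). The documents support neither share.

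**Conclusion.** The point holds as a matter of interpretation, with moderate severity. As written, relief after a second course can be credited to 1 x 8 Gy at week 6 and in time to pain response, in one arm only, and the bias runs toward no difference.

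Its size cannot be derived from the documents. Under slow-acting assumptions it costs 1 to 2 points of power; a 1.5-point rise costs about 8 and a 3-point rise about 18. The direction rests on a second course not worsening the week-6 score. The two-week gap rests on counting week 6 from treatment.

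Two further inferences are not supported: that the sample size is wrong, since it reproduces, and that the primary analysis must be replaced by a non-responder rule, since that rule has its own one-sided error.

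**What to change.** In Statistical analyses:

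1. Keep the comparison of week-6 scores as observed. Prespecify beside it an analysis in which any patient, in either arm, who receives further local treatment at the study level before the week-6 score counts as a non-responder.
2. State that the two analyses bracket the single-dose contrast, and that a null as-observed result alone does not show that one 8 Gy dose is as good.
3. For time to pain response, treat re-irradiation as a competing event, so that a later improvement is not counted as a response to the randomised course.
4. Record the date of any re-irradiation by week 6 rather than relying on the 3-monthly collection.

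The cost is a few sentences and one date field, with no extra patients. The downside is that the non-responder analysis in practice penalises only the 8 Gy arm and is anti-conservative if slow responders are re-irradiated early, as step 5 of the working shows. It should not be the sole primary test.

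The clinical team should also reconcile the 4-week mark in Radiotherapy, the 4-to-6-week response time in Background and Discussion, and the 6-week time point with its two origins in the Abstract and Statistical analyses. No clinical rule is proposed here.

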### Statistical analyses

The primary outcome of interest in this study is a reduction of pain of 2 points at 6 weeks since baseline. The literature shows that in patients with conventional radiotherapy the percentage of patients with pain reduction ranges from 66 % to 72 %. We assume that the percentage of patients with pain reduction is 70 % in the group with conventional radiotherapy compared to 85 % in the group with stereotactic radiotherapy. Therefore, 135 patients are needed in each group to obtain a power of 80 % (Fisher-exact test, two-sided, alpha = 0.05). We adjust for a drop-out rate of 30 % and will include a total of 386 patients. The primary analysis will be the comparison between the two treatment arms of the proportion of patients with pain reduction, defined as a decrease in pain score of at least 2 points from initial pain score, at 6 weeks. Time to pain progression, radiation-induced fracture and/or death will be calculated from date of randomization to the documentation. For the calculation of response, no fixed time interval from the date of randomization will be applied. Response of treatment will be calculated if at least two successive follow-up pain scores are available.

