### Recruitment and randomization

Patients must be able to undergo radiotherapy and fulfill the eligibility criteria. The diagnosis of a solid tumor must be pathologically confirmed to make the patient eligible for the study. The extent of the metastases in the spine should be visualized on an MRI, no longer than two weeks before randomization or no longer than 6 weeks before the start of treatment. To determine the clinically relevant category of stability, the Spinal Instability Neoplastic Score (SINS) will be obtained and documented prior to treatment. Earlier studies showed that the sensitivity of SINS for potentially unstable or unstable lesions was 95.7 %, with a specificity of 79.5 % [14, 15]. Written informed consent will be obtained from all participants before entering the study.

The study is designed to be carried out in multiple centers in the Netherlands. Patient randomization will only be allowed from authorized investigators, their authorized staff members, or data manager. A patient can be randomized only after verification of eligibility. In case a patient is eligible and a written informed consent is obtained, the randomization form must be faxed or digitally sent to the Data Center. Randomization will be performed using a password-protected database (OpenClinica). Patients will be stratified on primary tumor type (breast/prostate, non-small-cell lung/renal/colorectal/sarcoma/melanoma and others), Karnofsky performance status (60 to 70 versus 80 to 100) and number of spinal metastases (single lesion, 2 to 3 lesions, and disseminated osseous lesions).

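### The primary analysis is described as a plain comparison of two proportions, with Fisher's exact test the only test named: valid and adequately powered, but conservative and less efficient than an analysis using the stratification factors and baseline pain

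*Protocol article*

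**What the plan says.** Under Recruitment and randomization: "Patients will be stratified on primary tumor type" (three groups), and also on "Karnofsky performance status (60 to 70 versus 80 to 100) and number of spinal metastases" (three groups). That makes 3 × 2 × 3 = 18 cells.

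Under Statistical analyses, the sample size assumes that "the percentage of patients with pain reduction is 70 % in the group with conventional radiotherapy", "compared to 85 % in the group with stereotactic radiotherapy". It concludes that "135 patients are needed in each group" "to obtain a power of 80"%, with the test given in parentheses as "Fisher-exact test, two-sided, alpha = 0.05". Allowing for 30% drop-out gives 386 patients in total.

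The analysis itself is described in one sentence: "The primary analysis will be the comparison between the two treatment arms of the proportion of patients with pain reduction". Response there is a fall of at least 2 points from the initial pain score at 6 weeks. The sentence names no test or model and mentions neither the stratification factors nor baseline pain.

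**The concern.** When allocation is balanced within prognostic strata, the difference between two crude proportions varies less than a test that ignores the strata assumes. Such a test then rejects too rarely under the null. Fisher's exact test adds conservatism of its own because of the discreteness of the table.

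Baseline pain matters for a separate reason. Patients qualify with a score of 2 or more, and response needs a 2-point fall. A patient entering at 2 must reach 0, while one entering at 8 need only reach 6. Baseline pain is therefore tied to the endpoint by construction. It is collected in everyone, yet it is not a stratification factor, so the design does not balance it.

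The stake is efficiency. The margin is worth having because the power target depends on a 15-point difference, and the protocol itself quotes control rates from 66% to 72%. At 72% versus 85%, exact power with 135 per group is 69.6% for Fisher and 75.0% for chi-square.

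**Working it through.** **Inputs from the protocol article.** Response rates 0.70 and 0.85; two-sided alpha 0.05; power 80%; 135 per group; 30% drop-out; 386 in total; 18 strata.

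**Step 1: reproduce the plan's figures.** The normal-approximation formula is

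n = [z₀.₉₇₅ √(2p̄(1−p̄)) + z₀.₈₀ √(p₁(1−p₁) + p₂(1−p₂))]² / (p₂−p₁)², with p̄ = 0.775.

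This is [1.960 × √0.34875 + 0.842 × √0.3375]² / 0.0225 ≈ 120.5, so 121 per group. The continuity correction, n/4 × [1 + √(1 + 4/(n × 0.15))]², gives 133.5, so 134. Full enumeration of the two-sided Fisher test at 135 per group gives power of 80.99%. With drop-out, 270/0.70 = 385.7, so 386. The stated 135 and 386 are correct for Fisher's test.

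**Step 2: Fisher against chi-square, exact, 135 per group.** No assumption about prognosis is needed here.

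| Quantity | Fisher | Pearson chi-square |
|---|---|---|
| Size, common rate 70% | 3.7% | 5.1% |
| Size, common rate 77.5% | 3.5% | 5.1% |
| Power, 70% vs 85% | 81.0% | 85.0% |

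The exact test therefore costs 85.0 − 81.0 = 4.0 points. In patients, 121 rather than 135 per group would be 242/0.70 = 345.7, so 346 in total against 386.

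**Step 3: add the strata.** The simulation used 20,000 trials per setting, 135 per arm, balanced allocation within the 18 cells, and marginal rates held at 70% and 85%. It compared both unstratified tests with a Cochran-Mantel-Haenszel (CMH) test over the strata. The document gives neither the stratum shares nor the spread of log-odds of response across strata, so both are assumptions and the spread is varied. The Monte Carlo standard error for power is about 0.25 points.

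| Log-odds SD across strata | Power: Fisher | Power: chi-square | Power: CMH | CMH − chi-square | Size: Fisher | Size: chi-square | Size: CMH |
|---|---|---|---|---|---|---|---|
| 0 | 81.0% | 85.2% | 84.9% | −0.3 | 3.9% | 5.3% | 5.2% |
| 0.25 | 81.2% | 85.3% | 85.1% | −0.2 | 3.6% | 4.9% | 4.9% |
| 0.5 | 81.4% | 85.4% | 86.0% | +0.6 | 3.5% | 4.7% | 5.0% |
| 0.75 | 81.9% | 85.9% | 87.3% | +1.4 | 2.7% | 3.8% | 4.9% |
| 1.0 | 82.7% | 86.7% | 89.7% | +3.0 | 2.2% | 3.1% | 4.7% |

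Stratifying adds almost nothing up to an SD of 0.5 and about 3 points at 1.0.

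**Step 4: adjusted logistic regression.** A model with arm, the three factors as main effects and baseline pain reaches about 86% power when nothing is prognostic. It reaches 87 to 91% under assumed moderate to strong effects, with size near 5%. Set against chi-square at 85 to 87%, adjustment adds roughly 0 to 4 points.

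**The case against.** The strongest objection is that the article does not fix an unadjusted Fisher test as the primary analysis. Fisher appears only in the sample-size parenthesis, and the analysis sentence gives an outcome and a contrast. An article condenses a fuller protocol, and adjustment is often left to that protocol or to the analysis plan. This stands as a limit on what can be claimed: the unadjusted Fisher analysis is a reasonable inference, not a stated fact. It does not remove the point. The section does describe the primary analysis, as a comparison of two proportions beside a single named unstratified test, and a better analysis is available from data already collected.

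A reader might go further and infer any of the following. The documents do not support them.

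- **The trial is underpowered, or wastes power it has paid for.** The sample size was calculated for Fisher, so its conservatism is already covered and 81.0% is delivered. What is forgone is power above the target.
- **The test is invalid.** It keeps the type I error below 5%.
- **Ignoring the strata is the main cause.** About 4 points come from the exact test alone. The part due to stratification is smaller and depends on assumptions.
- **The confidence interval is too wide.** The article specifies no interval.
- **Chance imbalance in baseline pain biases the result.** Such imbalance adds noise to a randomised comparison; it is not systematic bias.

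**Conclusion.** The point holds as one of efficiency and clarity. It is not an error in the design or its figures, which reproduce.

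Two results rest only on the protocol's own inputs: Fisher's size of about 3.5 to 3.7% at common rates of 70 to 77.5%, and the 4-point power difference from chi-square. The further 0 to 4 points from adjustment, and the fall in Fisher's size to about 2.5% (2.7% at SD 0.75, 2.2% at SD 1.0), depend on assumed stratum shares and prognostic strength. Confidence is therefore high on the direction and on the exact-test component, and moderate on the size of the adjustment component.

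The change is worth making because it costs almost nothing and gives some protection if the true difference is a little below 15 points.

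**What to change.** Before unblinding, state the primary analysis explicitly:

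- logistic regression of week-6 response on treatment arm, tumour type, Karnofsky category, number of spinal metastases and baseline pain score;
- stratification factors as main effects only, because 270 evaluable patients over 18 cells average 15 per cell and some cells will be sparse;
- treatment effect tested by likelihood ratio, two-sided at 0.05;
- effect reported as a standardised risk difference with 95% CI, so that the result stays on the scale of the 70% and 85% assumptions;
- Fisher's exact test kept as a supportive analysis.

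If the full protocol or analysis plan already specifies an adjusted analysis, it is enough to confirm that.

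The cost is a short change of wording, with no new data and no change to 135 per group or 386 in total. One detail must be settled. The Assessment of the endpoints section collects average, worst and present pain, and the Statistical analyses section does not say which of them is the initial score. The baseline covariate must be the same item that defines the 2-point drop.
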